### Risk–benefit analysis

All participants will be monitored and questioned for side effects. Both probiotics and prebiotics are safe for the majority of the population, but side effects can occur. Side effects of probiotics and prebiotics are usually minor and consist of self-limited gastrointestinal symptoms, such as a temporary increase in gas, mild abdominal discomfort, bloating, diarrhea, and constipation. Side effects can vary from mild to very serious and may vary from person to person. In some cases, these effects might be long-lasting, or permanent, and may even be life-threatening.

Food allergy symptoms (such as tingling or itching in the mouth; hives; swelling of the lips, tongue or other body parts; abdominal pain; diarrhea, or lightheadedness) may be experienced within a few minutes to 2 h after consuming the probiotic and prebiotic supplement if the participant is allergic to any of its ingredients.

Synbiotics (products containing a mixture of probiotics and prebiotics) are generally considered safe, particularly in healthy people; however, there are some risks. These risks are increased in participants who have compromised immune systems or have other serious medical conditions. Possible harmful effects can include developing infections or antibiotic resistance, or the production of harmful by-products from microorganisms contained in the synbiotic.

The risks of adverse events associated with this study are minimal, and any adverse events will be recorded and managed following Good Clinical Practice (GCP) guidelines and legal requirements. However, this study will provide important outcomes regarding the potential benefits of synbiotic consumption on physical function, strength and body composition, which may provide supporting evidence for the use of synbiotics as a cost-effective supplement for older individuals. Participants will be fully informed about the risks associated with the study before providing informed consent and will have the right to withdraw at any time. This will be explained in the ICF document and verbally during the screening process.

### Safety reporting

To ensure ongoing participant safety, at each visit, the research team will ask about any symptoms they have developed or any changes to their health that may have resulted from the IP. An adverse event (AE) will be defined as any untoward medical occurrence in a participant administered IP that does not necessarily have a causal relationship with the intervention [81]. An AE can be any unfavorable and unintended sign (including an abnormal laboratory finding), symptom or disease occurring, which appears to be associated with the administration of the IP. All AEs and serious adverse events (SAEs) that are deemed related to a participant’s involvement in this study will be collected, recorded, and reported to the authorizing ethics committee, following local requirements. A SAE will be defined as an adverse event that:Is life-threatening (places the subject at immediate risk of death).Requires in-patient hospitalization or prolongation of existing hospitalization.Results in persistent or significant disability/incapacity.Results in death.

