**Fig. 1 Fig1:**
[figure not shown]
Schedule of enrolment, interventions, and assessments (adopted from SPIRIT 2013 Figure). ^1^include age, gender, COVID-19 history and vaccine status; ^2^include heart rate, and blood pressure; ^3^include handgrip strength, 4m gait speed, balance testing, repeat chair stands, timed up and go; ^4^via bioelectric impedance analysis; ^5^include SARC-F, Physical Activity Scale for the Elderly, Gastrointestinal Symptom Rating Scale, Constipation Assessment Scale; ^6^include stool sample and blood sample. IP: investigational product

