#### Study duration

Participant involvement will be approximately 22 weeks. This will consist of a screening period of no longer than 2 weeks, a 16-week intervention period, and a 4-week follow-up period. Each participant will attend a screening visit, during which eligibility will be confirmed and informed consent will be obtained. Study investigational product (IP) will be initiated within 2 weeks following successful screening (at baseline visit). Each participant will subsequently attend 3 further visits: mid-intervention at 8 weeks, an end-of-intervention visit at 16 weeks, and a follow-up visit at 20 weeks. Study endpoints will be evaluated at each visit as discussed below. The trial design is outlined in Fig. 2.

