### Compliance with study intervention

Participants will be instructed to take their allocated study intervention once daily for 16 weeks. At week 8 (mid-intervention) and week 16 (end-of-intervention), participants will be asked to return their study IP (including unused supplements and empty packaging). IP accountability will be performed to confirm compliance with the required dosing schedule. In addition, participants will be asked to complete and return a study supplement adherence log, which will be reviewed in week 8 and 16 visits.

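### Tolerability is defined as the absence of adverse events and laboratory changes, and the two gut-symptom scales already scheduled are not named as tolerability outcomes

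*Protocol article*

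**What the plan says.** Under Objectives, the protocol article makes safety and tolerability a stated aim. Its Risk–benefit analysis section describes the expected side effects as "usually minor and consist of self-limited gastrointestinal symptoms, such as a temporary increase in gas, mild abdominal discomfort, bloating, diarrhea, and constipation". It adds that food-allergy symptoms "may be experienced within a few minutes to 2 h after consuming the probiotic and prebiotic supplement".

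On capture, the Safety reporting section says that "at each visit, the research team will ask about any symptoms they have developed". Under Study duration, the product starts at the baseline visit and the later visits are "mid-intervention at 8 weeks, an end-of-intervention visit at 16 weeks, and a follow-up visit at 20 weeks". The participant-held record that the article describes is "a study supplement adherence log, which will be reviewed in week 8 and 16 visits".

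On outcomes, Safety outcome measures lists the metabolic panel, the blood count, AEs and SAEs. The safety hypotheses (Hypotheses and study endpoints, Safety aims) define safe and well tolerated as the absence of changes or events in those same four categories.

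The caption of Fig. 1 says that the scheduled questionnaires "include SARC-F, Physical Activity Scale for the Elderly, Gastrointestinal Symptom Rating Scale, Constipation Assessment Scale". SARC-F has its own outcome section. The two gut scales are named nowhere else in the article.

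**The concern.** The harms that the article leads one to expect are short-lived and mild, while the described enquiry during dosing comes at long intervals. Symptoms from the first days of dosing may be forgotten, thought too trivial to mention, or given an uncertain onset date. Onset dates matter because the Relationship to study intervention section relies partly on timing to decide whether an event is related.

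The definition of tolerability adds to this. Because it asks for absence, incomplete capture pushes the result towards the hypothesis. Because it states no comparison with placebo, it also does not separate product effects from the background gut complaints of people aged 60 to 85. A conclusion that the product is well tolerated could then partly reflect weak capture.

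Two scheduled questionnaires could supply a graded, randomised comparison of gut symptoms, but the article gives them no role in the safety aim.

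**Working it through.** The plan gives no figure of its own on this point to reproduce.

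**1. Interval between enquiries.** Visit weeks (Study duration): 0, 8, 16, 20.
- Gaps: 8 − 0 = 8, 16 − 8 = 8 and 20 − 16 = 4 weeks, that is 56, 56 and 28 days.
- Dosing lasts 16 weeks, so both gaps during dosing are 56 days.
- Days from onset to the week 8 enquiry: onset on day 1, 56 − 1 = 55; day 7, 56 − 7 = 49; day 14, 56 − 14 = 42.

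**2. Expected harms set against the outcome lists.**

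| Expected harm (Risk–benefit analysis) | Scheduled scale (Fig. 1 caption) | Named in Safety outcome measures or Safety aims? |
|---|---|---|
| Gas, discomfort, bloating, diarrhea | Gastrointestinal Symptom Rating Scale | No; only as AEs |
| Constipation | Constipation Assessment Scale | No; only as AEs |
| Allergic symptoms | None | Only as AEs |

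The match in the first two rows is inferred from the titles of the scales. The article does not list their items or the period each one asks about.

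**3. Direction of the error.** The hypothesis is supported when nothing is recorded. A symptom that occurred but was not recorded can therefore only help it. A between-arm difference on a scale that every participant completes does not have this property.

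**4. Precision of a between-arm comparison.** Inputs from Statistical analyses and power: 37 per arm and about 30% dropout.
- Completers per arm: 37 × 0.70 = 25.9, taken as 26.
- Unadjusted 95% half-width, in SD of the score: 1.96 × √(2/26) = 1.96 × 0.277 = 0.54.
- Adjusted for baseline with correlation r, multiply by √(1 − r²):
  - r = 0.3: 0.954, giving 0.52 SD
  - r = 0.5: 0.866, giving 0.47 SD
  - r = 0.7: 0.714, giving 0.39 SD
- A change score without baseline adjustment has the factor √(2(1 − r)). At r = 0.3 this is √1.4 = 1.18, giving 0.64 SD, which is wider than the unadjusted follow-up comparison. This is why adjustment should be specified.

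The article's correlation of 0.7 concerns physical performance measures. Nothing in it supports a value for gut-symptom scores, so r is shown as a range.

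**The case against.** The strongest reply is that the article does not make the visit question the sole route:
- Risk–benefit analysis says that participants will be monitored as well as questioned.
- The AE collection period runs from consent to week 20.
- The withdrawal section promises attention to well-being for the whole study.
- The SAE clock starts when information is received, not at a visit.

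The full protocol is not shown and may describe contact between visits. These points stand. A reader might infer that symptoms are elicited only at visits and that early reactions are therefore missed, but the documents do not support that. They support a risk of under-reporting and poor dating.

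A reader might also infer that tolerability rests on recall alone. It does not, because two of the four criteria are laboratory panels, and SAEs such as hospitalisation depend less on memory than brief bloating does. Nor should the 56-day gap be added to the 7-day SAE clock as an expected reporting delay. That would need an SAE at the very start of dosing that nobody disclosed before week 8.

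On the scales, the figure is not shown, so their timing is unknown. The Physical Activity Scale in the same caption also lacks an outcome section, so condensation of the article may explain part of the silence, and the analysis may be set out elsewhere. That is fair, but the article does fix both the safety outcomes and the definition of tolerability, and the gut scales are in neither.

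Finally, a half-width of 0.54 SD is not precise. That is true, and the comparison would not establish equivalence. It would still show which differences between arms the data can and cannot exclude, which a definition by absence does not.

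**Conclusion.** The point holds in a limited form. The described active enquiry during dosing is 56 days apart, the expected gut symptoms are mild and transient, and the stated definition of tolerability rewards incomplete capture and has no comparator. Two scheduled scales that appear to match those symptoms are left out of the safety outcomes and the definition.

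This is an inexpensive improvement to how the safety aim is answered. It is not an arithmetical error or a contradiction in the plan, and it does not show that events will go undetected.

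The conclusion assumes that the scales are collected at baseline and at one or more later visits, and that they cover what their titles suggest. The precision figures assume equal dropout of about 30% in each arm and a normal approximation: 0.54 SD unadjusted, and about 0.52 to 0.39 SD adjusted for r from 0.3 to 0.7.

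**What to change.** Before unblinding, add to Safety outcome measures and to the Safety aims, as tolerability outcomes, the between-arm difference in change from baseline on the Gastrointestinal Symptom Rating Scale and on the Constipation Assessment Scale. Specify adjustment for the baseline score, the post-baseline visits at which the scales are collected, and a 95% confidence interval for each difference. Report these beside the AE, SAE and laboratory results by arm, so that the tolerability conclusion does not rest on absence alone.

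The cost is a short amendment and two extra tables from data already scheduled, with no added visit or participant burden.

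The change has limits. It does not shorten the 8-week interval or cover allergic reactions, and it may not recover episodes that resolved before the visit. Adding a symptom diary or text-message prompts is not recommended now. Enrolment was expected to reach its target in April 2024, so few participants would benefit early in dosing. Event ascertainment would differ between early and late enrollees, and staff would have to review the replies.

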### Safety outcome measures

Serum and plasma samples will be analyzed by an external commercial pathology facility to determine changes (outside normal variation) in clinical chemistry (Comprehensive Metabolic Panel [CMP]) and clinical hematology markers (Complete Blood Count [CBC]) elicited after baseline and through week 16. Adverse events (AEs) and serious adverse events (SAEs) will be assessed and recorded from baseline through week 20.

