### Relationship to study intervention

The principal investigator (PI) will assess all AEs and SAEs to determine whether there is any potential relationship to the study intervention. The relationship will be assessed as either “related” or “unrelated” as below:*Related*: There is a reasonable possibility that the study intervention caused the AE or SAE, or there appears to be a temporal relationship between the administration of the study intervention and the event.*Unrelated*: There does not seem to be a reasonable possibility that the administration of the study intervention caused the AE or SAE, there does not appear to be a temporal relationship between the study intervention and event onset, or there has been an alternate etiology established that explains the event.

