### AE and SAE reporting

All AEs and SAEs will be captured on the *adverse events log*.

The PI will be responsible for notifying the approving HREC of any SAE, independent of the relatedness to the study, within 7 calendar days upon initial receipt of the information. If the SAE is considered as related to the IP, a report must follow within 7 days of learning about the SAE.

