### Period for collecting AEs/SAEs

The period for collecting AEs and SAEs (“active collection period”) for each participant is as follows:AEs: From informed consent until the end of study involvement (week 20).SAEs: From informed consent until study completion.

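### The adverse event rules conflict on what is recorded (events deemed related, or all events) and on the recording window (from baseline or consent; SAEs to week 20 or study completion)

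*Protocol article*

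**What the plan says.** All references are to the protocol article.

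**What is recorded**
- Safety reporting: "All AEs and serious adverse events (SAEs) that are deemed related to a participant’s involvement in this study will be collected, recorded, and reported" (recipient: the authorizing ethics committee). The same section defines an AE first without any need for a causal link, then describes it in a second sentence as something apparently associated with taking the product.
- Risk–benefit analysis: "any adverse events will be recorded and managed following Good Clinical Practice (GCP) guidelines and legal requirements".
- Relationship to study intervention: the principal investigator "will assess all AEs and SAEs to determine whether there is any potential relationship to the study intervention", with two classes, related and unrelated.
- AE and SAE reporting: "All AEs and SAEs will be captured on the" adverse events log. The ethics committee is to be notified of "any SAE, independent of the relatedness to the study, within 7 calendar days upon initial receipt of the information".

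**When it is recorded**
- Safety outcome measures: "Adverse events (AEs) and serious adverse events (SAEs) will be assessed and recorded from baseline through week 20".
- Period for collecting AEs/SAEs: "AEs: From informed consent until the end of study involvement (week 20"). SAEs run from consent to study completion.
- Hypotheses and study endpoints, Safety aims: the synbiotic counts as safe and well tolerated if there are no AEs after baseline through week 20 and no SAEs until study completion.

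**The concern.** In the Safety reporting sentence the condition of being deemed related governs collecting and recording as well as reporting. Staff who follow it would leave out events judged unrelated. Staff who follow the log rule would include them. Both instructions are in the current text.

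This matters because safety is a stated aim and its hypothesis is framed as the absence of AEs. What counts as a recordable AE therefore helps decide the answer, and a relatedness filter at entry can only move it towards safe. Attribution case by case is also a weak way to find an excess of events that are common in older people anyway, such as the infections named as a possible harm under Risk–benefit analysis. Comparing all events by arm is what shows such an excess, and events never recorded may not be recoverable later.

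The window conflict is smaller, but it leaves the period of observation behind the AE and SAE counts unclear.

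**Working it through.** The plan gives no figure to reproduce here, so the check sets the sections side by side. The only arithmetic is on the windows.

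**1. Scope of recording**

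| Section | Events recorded |
|---|---|
| Safety reporting | those deemed related |
| Risk–benefit analysis | any AE |
| Relationship to study intervention | all AEs and SAEs assessed, including an unrelated class |
| AE and SAE reporting | all AEs and SAEs, on the log |

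An unrelated class can be filled only if unrelated events are captured first. Three sections therefore point to full capture and one sentence to partial capture.

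**2. Could Safety reporting be only an ethics-reporting rule?** That reading removes the conflict over recording but not the one over reporting. For SAEs, Safety reporting would send related events to the committee, while AE and SAE reporting sends all of them. The two sections still disagree.

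**3. AE definition.** The first sentence needs no causal link. The second speaks of an apparent association with the product. Someone completing the log has two descriptions of what qualifies. The first sentence also speaks of a participant who has been given the product, so with collection from consent the period opens before an event can meet the definition.

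**4. Start of the window.** Inputs are from Study duration: screening of at most 2 weeks, with consent taken at the screening visit; 16 weeks of intervention; 4 weeks of follow-up.
- From baseline: 16 + 4 = 20 weeks.
- From consent: up to 2 + 16 + 4 = 22 weeks.
- Difference: at most 2 weeks, and 2/22 = 0.09, or about 9% of the longer window.

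These extra weeks precede first intake, so they bear little on the between-arm comparison.

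**5. End of the window for SAEs.** It is week 20 under Safety outcome measures, and study completion under both the collection-period section and the safety hypotheses. The article does not define study completion, so the size of this gap cannot be given.

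**6. Size of the possible loss.** The article gives no expected AE rate and no expected share judged unrelated. The loss runs from zero (log rule followed) to every event judged unrelated (Safety reporting followed as written). If the same share were dropped in both arms, the ratio of event counts would not change, but the counts and their absolute difference would shrink by that share.

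**The case against.** The strongest reply is that the sentence in Safety reporting was meant as a reporting rule. It ends with the ethics committee and local requirements, an event has to be captured before anyone can deem it related, and three other sections call for full capture. This stands to the extent that loss of unrelated events cannot be called the plan. It does not remove the conflict in wording, nor the disagreement over which SAEs go to the committee.

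Site staff who collect data are blinded, which makes filtering that differs by arm less likely. That also stands, but blinding does not recover events that were left out.

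A reader might draw several stronger conclusions that the text does not support:
- *Visits ask only about effects of the product.* The visit question also covers any symptoms that have developed.
- *The definition requires an association with the product.* The second sentence says what an AE can be, which is permissive. It sits badly with the first sentence but does not replace it.
- *Pre-dose events enter the safety comparison.* The hypothesis window after baseline can be an analysis window inside a longer collection period. The true conflict on the start is between Safety outcome measures and the collection-period section.
- *The second ethics-committee sentence on related SAEs is empty.* It may describe a separate report that follows the first notification.
- *Bowel symptoms and falls would be lost.* The schedule of assessments (Fig. 1 legend) lists the Gastrointestinal Symptom Rating Scale and the Constipation Assessment Scale, and SARC-F, with its falls item, is completed at each visit. These partly capture such events without a relatedness filter.
- *A given fraction, such as half, of the safety data is lost.* Nothing in the article supports any fraction. A temporal relationship alone is enough for an event to be classed as related, which could make the unrelated share small.

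**Conclusion.** The point holds as an internal contradiction that should be corrected. Safety reporting conflicts with Risk–benefit analysis, Relationship to study intervention, and AE and SAE reporting on which events are recorded, and with the last of these on which SAEs the ethics committee receives. Safety outcome measures conflicts with the collection-period section on the start of recording, by up to 2 weeks, and in wording on the end for SAEs.

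A reader might infer that harms judged unrelated never enter the dataset. The document does not establish that, since most of it favours full capture. The supported conclusion is conditional: if the Safety reporting sentence is applied as written, events judged unrelated are missing from the between-arm comparison, and the hypothesis of no AEs is biased towards safe by an amount that the document does not allow one to compute. The scope conflict is the important part; the start-date conflict is minor for comparing arms.

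The SAE end-date conflict depends on what study completion means. The collection-period section sets its periods per participant, so a reader who takes the phrase to mean the end of the whole trial goes beyond the text. If it means the participant's own last visit at week 20, the difference disappears, but the article does not say so.

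**What to change.** - **Scope.** Bring Safety reporting into line with the other three sections: record every AE and SAE with its onset date whatever its relatedness, and hold the relatedness judgement as a recorded attribute. State ethics-committee reporting in a separate sentence from recording.
- **Definition.** Remove the clause on apparent association with the product from the second AE sentence.
- **Window.** State one collection window, in the same words, in Safety outcome measures and in the collection-period section. Compare arms on events after first intake, as the safety hypotheses already imply, and list any events between consent and first intake separately.
- **To be reconciled by the sponsor.** The end date for SAEs (week 20 or study completion, with the latter defined), and the ethics-committee reporting sentences in Safety reporting and in AE and SAE reporting. The document does not show which version is intended.

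The cost is wording changes in these sections and a somewhat longer adverse events log. Sample size, visits and assessments do not change.
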